## Abstract

**Background:**

Prostate‐specific membrane antigen (PSMA)‐positron emission tomography/contrast‐enhanced computed tomography (PET/CT) is a sensitive imaging modality for prostate cancer (PCa). Due to lack of knowledge of the patient benefit, PSMA‐PET/CT is not yet recommended in the European guidelines for staging and treatment planning of patients with newly diagnosed PCa. We will investigate the potential difference in progression‐free survival (PFS) and quality of life (QoL) of using PSMA‐PET/CT versus sodium fluoride (NaF)‐PET/CT for staging and treatment planning in patients with newly diagnosed PCa.

**Study Design:**

This is a prospective randomised controlled multicentre trial carried out at three centres in the Region of Southern Denmark.

**Endpoints:**

The primary endpoint is PFS. Secondary endpoints are residual disease, stage migration, impact on treatment strategies, stage distribution, QoL and diagnostic accuracy measures.

**Patients and Methods:**

Patients eligible for the study have newly diagnosed unfavourable intermediate‐ or high‐risk PCa. A total of 448 patients will be randomised 1:1 into two groups: (A) a control group staged with Na[^18^F]F‐PET/CT and (B) an intervention group staged with [^18^F]PSMA‐1007‐PET/CT. A subgroup in the intervention group will have a supplementary blinded Na[^18^F]F‐PET/CT performed for the purpose of performing accuracy analyses. QoL will be assessed at baseline and with regular intervals (3–12 months) during the study period. Treatment decisions are achieved at multidisciplinary team conferences based on the results of the respective scans and according to current Danish guidelines.

**Trial Registration:**

The Regional Committees on Health Research Ethics for Southern Denmark (S‐20190161) and the Danish Medicines Agency (EudraCT Number 2021‐000123‐12) approved the study, and it has been registered on clinicaltrials.gov (Record 2020110469).

## BACKGROUND

1

Prostate cancer (PCa) is one of the most frequent cancer forms in men in developed countries with 1.4 million patients diagnosed in 2020 and approximately 375 000 deaths worldwide due to PCa the same year.^1^ The 5‐year relative survival rate approaches 100% for the vast majority (89%) of men diagnosed with PCa but drops to 30% for those diagnosed with stage IV disease.^2^

For primary staging, current guidelines recommend traditional imaging, including bone scintigraphy (BS) and contrast‐enhanced computed tomography (CECT). These are, however, rather inaccurate with reported sensitivities and specificities of 42%–80% and 82%, respectively.^3^, ^4^ BS reflects bone metabolism and may be replaced by the newer Na[^18^F]F‐positron emission tomography (PET) although this has not yet proven any added value.^5^

The transmembrane protein, prostate‐specific membrane antigen (PSMA), is expressed on the majority of PCa cells and has become a unique target for molecular imaging of PCa. PSMA ligands can be labelled with positron‐emitting isotopes such as ^18^F and ^68^Ga for imaging. The ^18^F isotope is beneficial regarding availability and production. PSMA‐1007 is only sparsely excreted in the urinary tract, making diagnostics in the pelvic region favourable.^6^

Accuracy studies of PSMA‐PET/CT for lymph node staging in the primary setting have reported moderate sensitivities (59%) and high specificities (93%), but most studies have been performed with a ^68^Ga‐labelled tracer.^7^, ^8^ It has recently been shown in a randomised prospective trial that [^68^Ga]Ga‐PSMA‐11 PET/CT had a 27% greater accuracy compared with conventional imaging with CECT and BS. Upstaging and management change were reported 22% and 13% more frequently for PSMA‐PET/CT compared with conventional imaging, respectively.^9^ Regarding the favourable [^18^F]PSMA‐1007‐PET/CT, a multicentre retrospective study has shown promising sensitivity and specificity for lymph node staging of 85.9% and 99.5%, respectively.^10^

The European guidelines report that it could be tempting to replace BS and CECT with PSMA‐PET/CT in initial PCa staging, but the clinical benefit of detecting metastases at an earlier time point is still undetermined. Therefore, it is argued that results from randomised controlled trials (RCTs) evaluating the management and outcome should be available before a decision can be made to treat patients based on the results of these tests.^11^ We are aware of neither previous studies, current studies nor studies being planned to evaluate the impact of replacing traditional imaging with up‐to‐date PSMA‐PET/CT on patient outcomes such as progression‐free survival (PFS) and quality of life (QoL).

This study aims to provide knowledge of the role of PSMA‐PET/CT in the primary staging of PCa to improve evidence‐based clinical decision‐making.

### Objectives

1.1

The overall aim of this project is to investigate the impact on PFS and QoL of using [^18^F]PSMA‐1007‐PET/CT for primary staging in PCa compared with Na[^18^F]F‐PET/CT. We will compare [^18^F]PSMA‐1007‐PET/CT (interventional imaging) with Na[^18^F]F‐PET/CT (conventional imaging at our centres) in a randomised controlled design with regard to PFS (primary endpoint), stage distribution, treatment strategy, frequency of residual disease and QoL (secondary endpoints). We aim to analyse the diagnostic accuracy, stage migration and change in treatment strategy for [^18^F]PSMA‐1007‐PET/CT compared with Na[^18^F]F‐PET/CT in a subgroup.

### Study design

1.2

This trial is a randomised controlled clinical trial following the Consolidated Standards of Reporting Trials (CONSORT) guidelines.^12^ A total of 448 patients (power calculation is in the statistical section) will be included and randomised into a control group (A) and an intervention group (B) (Figure 1 and Appendix A). Patients in Group A will be staged by Na[^18^F]F‐PET/CT, that is, CECT for lymph node and soft tissue metastases, and Na[^18^F]F‐PET for bone metastases according to current practice at our centres. Patients in Group B will be staged by [^18^F]PSMA‐1007‐PET/CT (including CECT) for lymph node, bone and soft tissue metastases. A subgroup of patients in Group B will have a blinded Na[^18^F]F‐PET scan with low‐dose CT (ldCT) for attenuation correction for the purpose of performing comparative accuracy analyses.

**FIGURE 1 bco2243-fig-0001:**
[figure not shown]
Flow chart for PRISMA‐positron emission tomography (PET). CECT, contrast‐enhanced computed tomography; CT, computed tomography; PCa, prostate cancer; PSMA, prostate‐specific membrane antigen.

### Eligibility criteria

1.3

The study population comprises men (aged 18 years or older) with newly diagnosed unfavourable intermediate‐ or high‐risk (including locally advanced) PCa^13^ or low‐risk PCa with clinical suspicion of metastases based on other findings (i.e., bone pain or suspicion of lymph node or bone metastasis on the magnetic resonance imaging [MRI] performed before prostate biopsies). The inclusion and exclusion criteria are listed in Table 1. Patients will be recruited from the three urologic departments in the Region of Southern Denmark and referred for imaging prior to treatment in the clinical set‐up. Scans will be performed in three nuclear medicine departments in the region.

**TABLE 1 bco2243-tbl-0001:** Inclusion and exclusion criteria for patient enrolment.

Inclusion criteria, all must be fulfilled	Exclusion criteria, any criterion fulfilled warrants exclusion
Has given informed consent to participate	Consent not given
Can read and understand provided patient information material in Danish	Inability to read and/or understand provided patient information material in Danish
Biopsy verified, newly diagnosed and untreated prostate cancer OR Biopsy performed because of clinically strong suspicion of prostate cancer	Previously given consent to this study withdrawn for any reason
Any, some or all of the following features: PSA ≥ 20 ng/mL OR Gleason score ≥ 4 + 3 OR Tumour stage cT2c or above as determined by digital rectal exploration and/or transrectal ultrasonography Suspicion of metastases as judged clinically, for example, bone pain	Staging by imaging not warranted as judged clinically
Staging by imaging is warranted	Allergy towards Na[^18^F]F, PSMA or other contents in the solutions
	Biopsy performed because of clinically strong suspicion of prostate cancer not confirming the diagnosis
	PSA value above 200 ng/mL

Abbreviations: cT2c, clinical stage T2c; PSA, prostate‐specific antigen; PSMA, prostate‐specific membrane antigen.

## METHODS

2

### Enrolment and randomisation

2.1

Patient recruitment will be carried out in a collaborative effort by the regional departments of urology and nuclear medicine. Patients will receive oral and written study information, and acceptance to participate is documented in signed consent forms. Consenting patients will be randomised and allocated into one of the study groups. Randomisation will be performed 1:1 into Groups A and B with stratification according to risk status of high, unfavourable intermediate and low risk with suspected metastases, respectively. The randomisation will be executed in the REDCap database software (https://projectredcap.org/).

### PET radiotracers

2.2

The [^18^F]PSMA‐1007 will be produced according to Good Manufacturing Practice (GMP) in laboratory facilities at the hosting nuclear medicine department at Odense University Hospital. The [^18^F]PSMA‐1007 will be distributed to the two collaborating nuclear medicine departments, Hospital Lillebaelt and Hospital South West Jutland. The radiopharmaceutical will be dosed 2 MBq/kg, minimum 150 MBq and maximum 300 MBq. Sodium fluoride (Na[^18^F]F) will be partly produced at the hosting nuclear medicine department at Odense University Hospital and partly in a different facility in Denmark (Skejby Hospital). For the Na[^18^F]F‐PET, we will use a fixed dose of 200 MBq. See Table 2 for tracer specifications.

**TABLE 2 bco2243-tbl-0002:** Radiopharmaceutical specifications.

	Specification	
Radiopharmaceutical	[^18^F]F‐PSMA‐1007	Na[^18^F]F
Radioactivity, total (GBq)	≤40.9	≤123.7
Product volume (mL)	18 ± 1	17 ± 0.5
Appearance	Clear and colourless (slightly yellow)	Clear and colourless (slightly yellow)
pH	6.5–8.5	5.0–8.5
Chemical purity		NA
Impurities, single (mg)	≤0.1	
Impurities, total (mg)	≤0.5	
Radiochemical purity (%)	≥95	≥98.5
Radionuclidic purity (%)	≥99.9	≥99.9
Sterility	No growth	No growth
Endotoxins (IU/mL)	<9.7	<10.3
[^18^F]F‐PSMA‐1007, mass (mg)	≤1.8 mg	NA
Residual solvents		NA
Ethanol (%)	≤10	
Dimethylsulfoxide (%)	<0.25	
Content of		NA
Tetrabutylammonium ion (mg)	≤2.6	
Sodium ascorbate (mg)	≤105	
Half‐life, *T*½ (min)	105–115	105–115
γ‐Spectrometry (KeV)	511	511
Shelf‐life (h)	5	10

Abbreviations: NA, not applicable; PSMA, prostate‐specific membrane antigen.

### Imaging techniques

2.3

The PET/CT scanners are state‐of‐the art scanners from GE (GE Discovery 710 and GE Discovery MI, Hospital South West Jutland; GE Discovery MI, Odense University Hospital) and Siemens (Siemens Biograph mCT Flow 64 and Siemens Biograph Vision 600 Edge, Hospital Lillebaelt). All patients will have a CECT (according to local guidelines for contrast administration) as performed clinically in these patients in each department. The [^18^F]PSMA‐1007‐PET/CT scans will be performed 60 min post injection of the tracer, and Na[^18^F]F‐PET/CT 30 min post tracer injection.

### Image interpretation

2.4

Experienced nuclear medicine physicians and radiologists will read the examinations, and the [^18^F]PSMA‐1007‐PET/CT scans will be evaluated according to Prostate Cancer Molecular Imaging Standardized Evaluation (PROMISE),^14^ where lesions in lymph nodes, bones and other tissues are categorised into five categories ranging from benign to malignant (Appendix B).

The Na[^18^F]F‐PET/CT scans will be evaluated according to a similar Likert scale for bone lesions. On the CECT, the lymph nodes in the pelvic region will be considered possibly malignant if more than 8 mm in short axis, round and with no fat in the hilum.^11^

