### Reference standard

2.5

Metastatic disease will be deemed without further imaging or examinations if the presentation is considered of typical morphology and pattern for PCa, especially considering lymph nodes and bones. In other tissues, metastases will also be suspected by a typical appearance, and biopsy will be intended only as a part of the clinical set‐up when possible and clinically relevant. Biopsies are not performed solely as a part of the study. Further imaging will be used as reference standard to confirm or exclude metastatic disease when clinically indicated (see Table 3).

**TABLE 3 bco2243-tbl-0003:** Reference standard.

	Metastases deemed
Any organ but the prostate gland	Pathology confirming metastasis
Lymph nodes	Equal to or more than 8 mm, round and with no fat in the hilum, for PSMA‐PET with uptake of PSMA
Bones	Marked uptake of activity with or without malignant morphology in CT and not related to joint with degenerative changes or a fracture, or malignant morphology with uptake
Liver	Biopsy if possible and clinically relevant, for PSMA‐PET with uptake of PSMA
Lung nodules—malignant	Biopsy if possible (and clinically relevant)
Disseminated disease	If disseminated disease with a typical pattern for prostate cancer, disseminated disease can be determined without further imaging or biopsy
Metastases	Further imaging supporting the suspicion of a metastasis

Abbreviations: CT, computed tomography; PET, positron emission tomography; PSMA, prostate‐specific membrane antigen.

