### Diagnostic accuracy and stage migration

3.1

The secondary endpoint of diagnostic accuracy and stage migration will be performed in a subgroup of patients within Group B where patients will act as their own controls. Hence, the comparison will be made for Na[^18^F]F‐PET/CT versus [^18^F]PSMA‐1007‐PET/CT for diagnosing bone, lymph node and soft tissue metastases. For this purpose, the CECT from the [^18^F]PSMA‐1007‐PET/CT will be used together with the blinded Na[^18^F]F‐PET scan, which will be performed with a ldCT for sparing radiation to participating patients. In the same subgroup, we will determine the rate of stage migration and change of treatment strategy. This will be performed in an MDT‐similar set‐up for research purposes only. In this MDT, clinical information about the patients and the blinded Na[^18^F]F‐PET/CT scans will be used to make a first decision on the treatment strategy, which will subsequently be compared with the clinically decided treatment strategy based on the [^18^F]PSMA‐1007‐PET/CT. Due to potential stage migration in the PSMA group, we expect a change of treatment strategy in a smaller group of patients.

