### Statistical analysis plan and sample size determination

3.2

Descriptive statistics will be done according to data type: mean ± standard deviation or median (range) for symmetrically and asymmetrically distributed continuous variables, respectively, as judged visually with histograms including approximating normal curves; and frequencies and percentages for categorical variables.

The analysis of time‐to‐event endpoints (PFS, overall survival) will comprise Cox proportional hazard regressions adjusted for group, risk status (high‐, intermediate‐ and low‐risk PCa) and centre. Graphical displays will comprise Kaplan–Meier plots including risk tables (i.e., patients at risk in each group) and the results of respective log‐rank tests. The analysis of QoL data will comprise the estimation of the group difference in a repeated measurement analysis. Descriptive analyses will be performed, and results presented by proportions. Continuous variables will be compared using a *t* test, and categorical variables using a chi‐squared test. Additionally, regression analysis will be used to identify associations within data. Accuracy assessments of Na[^18^F]F‐PET/CT and [^18^F]PSMA‐1007‐PET/CT will relate to sensitivity, specificity, positive and negative predictive values that will be judged upon the reference standard (Table 3). Exploratory, bivariate testing will consist of unpaired *t* tests, alternatively, Wilcoxon's rank sum test, on continuous variables and chi‐squared test, alternatively, Fisher's exact test, on categorical variables. The level of significance will be 5% (two‐sided). All analyses will be done with STATA/IC 17 (StataCorp, College Station, TX 77845, USA).

A total of 402 patients (201 in each arm) are sufficient to indicate a statistically significant difference in PFS with assumed hazard rates of 0.35 and 0.5 for [^18^F]PSMA‐1007‐PET/CT and conventional staging, respectively, implying a hazard ratio of 0.7. Estimates are based on a study duration of 4 years, consisting of 3 years of accrual time and a minimum follow‐up period of 1 year (two‐sample comparison of survivor functions; exponential test; power: 80%). Accounting for loss to follow‐up of 10%, a total of 448 patients (224 in each arm) will be included in the study.

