**Secondary endpoint**	
Na[^18^F]F versus PSMA in Group B	Accuracy of evaluating bone metastases; Stage migration; Treatment strategy

Abbreviations: PSMA, prostate‐specific membrane antigen; QoL, quality of life.

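### The CECT reading rule and the reference standard disagree on a pelvic lymph node of exactly 8 mm; if Table 3 is the common reference, this is a probably small bias against the NaF/CECT comparator

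*Protocol article*

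**What the plan says.** All references are to the protocol article.

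- **Section 2.4 (Image interpretation), CECT reading:** "the lymph nodes in the pelvic region will be considered possibly malignant if more than" a limit set at 8 mm across the short axis; a round shape and absence of hilar fat are also required. The inequality is strict, the axis is named and the rule is limited to the pelvis.
- **Section 2.5 (Reference standard), Table 3, lymph node row:** "Equal to or more than" 8 mm, with the same shape and hilum conditions and, for PSMA-PET, tracer uptake as well. The inequality is inclusive, and neither axis nor region is given.
- **Section 3.2:** sensitivity, specificity and predictive values of both examinations are measures "that will be judged upon the reference standard (Table 3").
- **Section 3.1:** the accuracy comparison is "for diagnosing bone, lymph node and soft tissue metastases", in a Group B subgroup where "patients will act as their own controls". The CECT acquired with the PSMA scan is combined with the blinded NaF-PET to form the comparator.
- **Section 1.2:** the nodal part of conventional staging is "CECT for lymph node and soft tissue metastases"; NaF-PET covers bone.
- **Appendix C:** the within-Group-B accuracy endpoint appears as "Accuracy of evaluating bone metastases", with no mention of nodes.

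**The concern.** The reading rule and the reference row use the same number and the same morphology but opposite treatment of the boundary. In the accuracy subgroup, one CECT supplies both the comparator's nodal reading and the node size that the reference row uses. A disagreement at 8 mm would then come from the wording of the rules and not from what the scan shows.

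The direction is fixed. Such a node with PSMA uptake counts for PSMA-PET/CT and against NaF/CECT, and the subgroup is sized to show superior sensitivity of PSMA-PET/CT. At stake is a small, avoidable part of that sensitivity difference. The differences in axis and region add to the ambiguity: the reference row can apply to nodes, or to a diameter, that section 2.4 does not address.

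**Working it through.** No figure stated in the article depends on the node threshold, so there is nothing to reproduce. The check sets the two rules side by side and then gives a scale.

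**1. The rules compared**

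| | Section 2.4, CECT reading | Table 3, lymph node row |
|---|---|---|
| Size | > 8 mm | ≥ 8 mm |
| Axis | short axis | not stated |
| Region | pelvic | not stated |
| Morphology | round, no hilar fat | round, no hilar fat |
| PSMA uptake | not applicable | required for PSMA-PET |
| Result | suspicious | metastasis |

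**2. A test case.** Take a round pelvic node without hilar fat, 8 mm in short axis, with PSMA uptake.

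- Reference row: 8 ≥ 8 is true, so the node is a metastasis.
- CECT reading: 8 > 8 is false, so the node is not flagged.
- With Table 3 as common reference, this is a node-level false negative for NaF/CECT.

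At 7 mm neither size condition is met, and at 9 mm both are. The inequality matters only at the boundary value.

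**3. From node to patient.** The sample size in section 3.2 is in patients. At that level the case is a comparator miss only if nothing else makes the patient positive on NaF/CECT.

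**4. Scale.** Inputs from section 3.2: 128 patients, 30% prevalence of metastases, assumed sensitivities 0.38 (conventional) and 0.85 (PSMA).

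- Expected patients with metastases: 128 × 0.30 = 38.4.
- Loss of comparator sensitivity for k affected patients, compared with a reading rule that would have flagged them: k / 38.4.

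| k (assumed; not in the documents) | Loss, percentage points |
|---|---|
| 0 | 0 |
| 1 | 2.6 |
| 2 | 5.2 |
| 3 | 7.8 |

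- Planned difference: 0.85 − 0.38 = 0.47, or 47 points.

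If the rules were instead aligned by moving the reference row, the patient would leave the reference-positive group and the shift would be smaller. For k = 1: 0.38 × 38.4 = 14.6 true positives, and 14.6 / 37.4 = 0.390, a change of about 1.0 point.

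**The case against.** Several points against the concern are fair.

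- **The role of Table 3 is not beyond doubt.** A reader might infer that every qualifying 8 mm node is a comparator miss by definition. The text does not go that far. The node row varies by modality, so it can be read as a positivity rule for each test. On that reading the 8 mm node is positive on CECT and there is no miss, although Table 3 then contradicts section 2.4 outright. Section 2.4 also sets a level of suspicion; the article does not say which reading counts as test-positive.
- **Size is not the only route.** Section 2.5 also admits pathology, typical pattern and further imaging, which may confirm or exclude metastasis, and section 2.6 sends doubtful cases for further work-up. No order of precedence is given, so the size row need not decide.
- **Reach.** If Appendix C governs, accuracy concerns bone only and the nodal mismatch does not touch that endpoint. Section 3.1 says otherwise, so this is unresolved.
- **Size of effect.** A reader might infer a material ceiling on comparator sensitivity, or a threat to the superiority claim. Neither is supported. The article gives no distribution of node sizes and no rounding convention, and even three affected patients (7.8 points) is small beside a planned gap of 47.
- **Staging.** A reader might infer that N stage in both arms needs one size cut-off. The documents point the other way: PSMA scans are read by PROMISE categories without a stated size threshold, and the Discussion expects PSMA to reveal nodes too small for CECT to detect. Imposing a cut-off there would remove part of the contrast under study and would set a clinical rule.

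These points limit the consequence. None removes the disagreement between the two stated thresholds.

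**Conclusion.** The concern holds as a minor internal contradiction. The two stated thresholds differ at 8 mm, and also in axis and region, and nothing in the article reconciles them.

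The bias against NaF/CECT rests on four conditions:

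- Table 3 is the common reference for both tests.
- Nodes are part of the accuracy endpoint.
- The node measures exactly 8 mm.
- No pathology or further imaging overrides the size criterion.

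Where all four hold, and the node is the patient's only reference-positive lesion, each such patient costs the comparator about 2.6 points of sensitivity. Their number is unknown from the documents and the overall effect is probably small. The 0 to 3 patients shown above is an assumed range for illustration, not an estimate.

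**What to change.** Reconcile section 2.4 and the lymph node row of Table 3 before the accuracy subgroup is analysed, so that the CECT reading rule and the size criterion of the reference use the same inequality, axis and nodal region. Which cut-off is right is for the investigators; this review does not choose one. The change should not add a size cut-off to PSMA-based N staging in Group B.

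The same edit can say whether the Table 3 node row is a common reference or a rule for each modality, and bring Appendix C and section 3.1 into line on whether nodes are in the accuracy endpoint.

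The cost is about one line in each place, with no change to the sample size. Whether scans already read need a second look depends on whether node diameters were recorded, which the article does not say.
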